### Healthcare professional perspectives

There are 12 paediatric palliative care networks in the UK, which include professionals from a range of organisations within paediatric palliative care. Several have patient and family representatives. Arrangements will be made to present study findings to four of the UK networks at existing meetings. The presentation will be followed by a structured focus group which will aim to first to test out and validate with palliative care professionals the themes from the research findings, and second aims to collect views of professionals. These multiple perspectives will inform and guide the formulation of recommendations for healthcare services in the future.^50^

An expression of interest email will be circulated to network chairs via Together for Short Lives, and arrangements made to attend meetings from networks who respond. Audiorecorded focus group discussions will be carried out at those meetings by SM.

### Patient and public involvement

PPI has been integral to the design and conduct of the study. Members of existing groups at a children’s hospital and children’s hospice have provided advice on the study proposal and design. Smaller groups have been recruited for specific activities, including conference presentations. Group members range in age from 12 to 22 years. PPI activities are outlined in table 4, and will continue throughout the project, with the aim of coproducing the recommendations for the model of care. This will involve structured group sessions during which anonymised findings of the data analysis will be presented to the group for feedback and comment. A patient experience framework will be used to structure the discussion and to build recommendations.^51^

**Table 4 T4:** PPI activities

Completed PPI activities	Developing the original research proposal. Advising on the language used in the study (suggesting a change in the title from ‘Palliative Care for Children and Young People: What? When? How?’ to ‘The Journey through Care’. Developing participant resources including leaflets for older and younger children. Interview design, including suggesting how questions could be phrased and asked. Providing family perspectives to a literature review, and becoming a coauthor on the paper.^18^ Taking part in oral presentations at regional conferences.
Work in progress	Designing conference posters and presentations for national conferences. Working as coresearchers to carry out a survey study to investigate understanding of the term ‘palliative care’ for children and young people and healthcare professionals.
Future plans	Working with a project-specific group to explore the findings of the research study and develop recommendations for a new model of care. Dissemination projects including conference presentations, posters, website design, use of social media, infographics and films.

PPI, patient and public involvement.

### Strengths and limitations

The strength of this study lies in the in-depth, contextual qualitative nature of the data, with multiple child and family member stories captured over time. Our anticipated study population is diverse in terms of age, clinical condition, cultural background and family structure, allowing detailed consideration of the role of healthcare services in effectively recognising and supporting children and families with their individual needs. All of the children and families included in the study could benefit from palliative care as it is currently defined,^15^ however, not all will have had conversations about this with their clinicians, or been referred to specialist palliative care services. Given the nature of their clinical conditions, including for some the inability to communicate verbally or deterioration in their health, recruitment and retention within the study is likely to become a challenge and will require a reflexive, flexible approach.

Potential limitations in the study include our exclusion of neonates, preschool children and young people at transition (over the age of 18 years). These groups all warrant research in their own right. Given the time and resource constraints of the study, all interviews will be carried out in English. Further research into the experiences of children and families who cannot communicate in English is necessary. There will be ongoing consideration of sources of bias. Recruitment bias is being addressed by aiming for a diverse sample and providing access to project information independent of the clinical teams. Data saturation will be sought during data analysis, with an ongoing process of reflection and peer review to address any possible unconscious bias of the researcher (SM).

### Ethics and dissemination

Research with children raises ethical and legal considerations around recruitment, consent and data collection.^52 53^ In addition, research regarding palliative and end-of-life care can be emotionally demanding and distressing for those involved. There are also particular ethical issues to consider given the longitudinal nature of the study.^54^

We are recruiting children and families who are potentially vulnerable and may be experiencing considerable distress. The justification for our approach is that children and their families in this situation are rarely asked about their experiences, but talking to them and understanding their experiences is essential in order to be able to design and develop services that respond to their actual needs. Here, we summarise our approach to the ethical issues the study raises (figure 1).

**Figure 1 F1:**
[figure not shown]
Ethical issues in longitudinal qualitative research for children and families in palliative care.

#### Language

Published literature suggests that the term ‘palliative care’ is poorly understood and perceived negatively,^55–59^ a view confirmed by our PPI group. The scope of our study is therefore to investigate the experiences of children with ‘life-limiting’, ‘life-threatening’ and ‘conditions which may or may not get better’, whether or not they have heard of palliative care or receive care from specialist services. ‘Palliative care’ will be avoided in participant information sheets and interviews, unless individuals are already familiar with palliative care services or bring it up themselves.

#### Recruitment

There is an ethical challenge in terms of potential coercion to the study by clinicians who know the family well. Clinicians will therefore only provide study information but will not actively recruit families; the initial expression of interest is from the family to the researcher. The researcher (SM) will then discuss the study in person or by phone with the child and their family member(s) and answer any questions before arranging a time for interview. Participants will be made aware that they can decline to take part or to withdraw at any stage without having to give a reason. Interviews are only carried out at a time that is mutually agreed and minimises any potential inconvenience or intrusion.

#### Equity of access to the study

Recruitment through clinical teams is widely used in palliative care research but may be limited by ‘gatekeeping’.^60^ There may also be families who wish to participate who do not find out about the study through their clinical team. In order to address this, we have designed posters for display on hospital wards and in outpatients, and at the local children’s hospice, and a paragraph for organisational newsletters. These provide the direct contact details for the researcher (email, text or phone).

The study setting is Birmingham, UK, a city where the population is highly diverse in terms of family situation and multiculturalism. Over 50% of families with a child known to palliative care services in Birmingham and Solihull are from black or minority ethnic backgrounds.^61^ Many of these families speak English as a first or second language, so within the time and resource constraints of this study, interviews will be carried out with those who can provide informed consent and take part in an interview in English.

#### Consent

Consent for the study raises ethical and legal issues with children who are under the age of 16 years and/or do not have the capacity to consent. We will aim for written and/or verbal consent and agreement from every individual for every interview.

For children under the age of 16, written consent will be obtained from the parent and then verbal or written agreement obtained from the child.

In keeping with the Mental Capacity Act, there is an assumption of capacity in young people aged 16 years and over, so they will be asked for consent first, followed by agreement from their parent(s). Parental agreement is not a legal requirement, but conducting an interview with a young person about a potentially difficult subject without the knowledge or agreement of their parents is an ethical concern. If there is a concern that the young person lacks capacity or is considered particularly vulnerable, for example, with a learning disability, parents will be asked to provide verbal and written consent in addition to the young person’s agreement.

Parental consent is required for any interview to be carried out in the family home.^53^

For a child on a full care order, social worker consent would replace that of parental consent. Where possible parental consent/agreement will also be sought.

#### Interviews

Subject areas discussed during interviews may cause distress to participants, and recruitment may occur soon after sensitive conversations. We have designed the study to ensure that the risks and burden associated with taking part in the study are minimal.

Qualitative interviews will be informal and reflexive to the needs of the participant. In the event that a participant experiences any difficulties during the interview, such as tiredness or distress, the interview will be halted, and if necessary brought to an end. Adequate time will be given for debrief, and the researcher will provide information about local resources for support if necessary. Interviews will be carried out at a time and in a location that is convenient to the participants. If this is in hospital, the researcher (SM) will liaise closely with clinical teams so that the research does not interfere with routine clinical care and ward work.

#### Longitudinal interviews

Family views and understanding of what might happen next as a result of the condition of the child will be discussed sensitively, and any follow-up interviews scheduled around possible further treatments. If it seems likely that there will be a deterioration in the condition of the child, this is explored carefully and an agreement made with the individual family about whether they want to continue to participate in the study.

#### Anonymity and confidentiality

All interview data will be anonymised with personal identifiers removed. Any qualitative interview data that could identify child, families or any professionals involved in their care because of the individuality and context of the narrative is included in the data analysis, but will be excluded from reporting.

Field notes and anonymised interview transcripts will be stored securely on a password protected university hard drive.

#### Minimising harm to the researcher

There is a need for clearly defined boundaries for a researcher–participant relationship in a longitudinal study of this type. It will be made clear to participants at the time of consent that it is not the role of the researcher to provide personal support or clinical advice. With the risk of emotional distress for the researcher, plans to ensure adequate support through regular academic supervision and access to a counsellor are in place.

#### Serious concerns and safeguarding

If information contained in a participant’s response indicates a serious clinical or safeguarding concern or an issue which may jeopardise the safety of the participant or another person, this will be escalated appropriately in line with the protocols of the community or hospital trusts. This may on very rare occasions necessitate a breach of participant confidentiality in order to maintain their safety. Participants will be informed of any disclosure and to whom it is made.

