## Methods and analysis

In order to conduct an exploration of the experiences of healthcare from the perspective of children with life-limiting and life-threatening conditions and their families, we will adopt qualitative research methods and a narrative-based approach, suitable for complex, emotionally charged subject areas.^39 40^ Active listening, reflection, a flexible approach and insight into the narratives being co-constructed between participant and researcher will be necessary throughout.

This is the protocol for an in-depth longitudinal qualitative study using semistructured interviews with school-aged children (5–18 years) and one or two of their household family members.

Benefits of longitudinal studies include being able to describe the changing needs of the children and their families, and their experience of services, over time,^41^ and enabling rapport to build between researcher and participant.

Neonates, preschool children and young people aged over the age of 18 years are excluded from this study. Specific issues around healthcare services arise when considering neonatal care and young people who are making the transition from paediatric to adult services, both of which warrant research in their own right. Research methods would need to be tailored to interview preschool children; this is also an area for potential future research.

The research plan has been informed by review of relevant literature, patient and public involvement (PPI) work and advice from local experts via the West Midlands Paediatric Palliative Care Network.

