### Interview plan

Interviews will be carried out by SM, a researcher who is also a general practitioner (GP) with advanced communication skills training and previous experience in qualitative interviewing. According to the preference of participants, interviews will be conducted with individuals, or with the child and parent together, in their preferred location. One or two family members will be interviewed in each family, either individually or together, depending on their preference and what is most convenient for them.

Interviews will be open and conversational, using a blended approach of interview techniques, with passive interviewing allowing the participant space and time to tell their story (narrative), and more active techniques, including appreciative inquiry, which asks ‘What works well?’ and ‘Why does it work well?’,^4 43^ employed. A topic guide (table 2) will guide the interview; this will continue to develop iteratively throughout the research, with adaptations made during each interview and in response to each individual participant.

**Table 2 T2:** Topic guide

For all families	For those aware of ‘palliative care’

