July 2016	“Remember young people who are seriously ill are more mature, they have to grow up” “Keep it simple as often a child will openly speak anyway” “‘Do you talk about it to your friends?’ is a good question, a good way to talk to most ages” “Children are more eloquent, mature and more capable than you think”
October 2016	“Use pictures and images, more emojis”
February 2017	“Doesn’t make me uncomfortable as I think it is very important and relevant”

PPI, patient and public involvement.

Each interview will be audiorecorded, with field notes made to include any additional comments from the child or family made once the audiorecording has stopped,^45^ reflections on the interview and observation of the family situation, environment, behaviour and any other interactions that may take place (for example, with other members of the family and clinical staff in hospital or on the phone).

Participants will be asked whether they would like to participate in interviews that will take place over a period of up to 12 months. These are intended to allow the identification of common themes over time and for theories generated through analysis of earlier interviews to be tested out during later interviews.^41^ The time intervals between interviews will be individually agreed, depending on the child and family circumstances. The method of communication with each family will also be individually agreed (phone or email). Up to three interviews with each participant are aimed for.

We anticipate practical challenges with conducting longitudinal interviews relating to fluctuations and changes in the clinical condition of each child. Depending on their condition, some children will respond well to treatments and get better. Others may suffer unexpected complications of their condition or treatment, and some may suffer deteriorations which bring about the possibility of dying. To manage the research in this context, we will check the family understanding of the situation before every interview. On occasions, interviews may need to be postponed and rearranged at late notice due to a change in circumstances.

For children who are unable to participate in interviews due to their condition, family members will be interviewed. Children and families are under no obligation to take part in follow-up interviews if they do not wish to. In these cases, and with their consent, data from previous interviews will still be included in the study.

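### The safeguarding section promises to tell participants of any disclosure, with no exception for a participant who is the subject of the concern

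*Protocol article*

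**What the plan says.** The rule is in the protocol article under Ethics and dissemination, subsection Serious concerns and safeguarding. It has three parts.

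- **Trigger and route.** It opens with "If information contained in a participant’s response indicates a serious clinical or safeguarding concern", extends to matters that put the participant or someone else at risk, and says "this will be escalated appropriately in line with the protocols of the community or hospital trusts".
- **Confidentiality.** "This may on very rare occasions necessitate a breach of participant confidentiality in order to maintain their safety".
- **Informing.** "Participants will be informed of any disclosure and to whom it is made".

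Two other places show whom the last sentence reaches. Methods and analysis describes "semistructured interviews with school-aged children (5–18 years) and one or two of their household family members". Interview plan adds that, as participants prefer, "interviews will be conducted with individuals, or with the child and parent together, in their preferred location".

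**The concern.** The final sentence covers any disclosure and states no exception. Telling a participant that confidence has been broken is a sound default, and the default is not in question. The difficulty is that this study enrols several people from one household, so the participant to be told may also be the person whose conduct gave rise to the report. Telling that person that a report exists, and who holds it, could raise the risk to the child before those responsible have acted.

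The section gives safety as its reason for breaking confidence. An unconditional duty to inform can defeat that reason in the cases where it matters most. The study population makes this more than a formality: the Consent subsection provides for children on a full care order and for young people thought to be particularly vulnerable.

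**Working it through.** No arithmetic applies. The check is to set the informing sentence beside the definition of participants and see what it requires in each situation.

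**Inputs**

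1. Duty to inform: any disclosure, including its recipient, with no stated exception (Serious concerns and safeguarding, last sentence).
2. Participants: the child and one or two household family members (Methods and analysis), interviewed singly or together (Interview plan).
3. Deference to trust protocols: attached to how a concern is escalated (Serious concerns and safeguarding, first sentence). The informing sentence carries no such qualification.
4. Stated purpose: maintaining safety (same subsection, second sentence).

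**Two readings of the word Participants in the last sentence**

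- *Broad*: any participant affected by the disclosure is told.
- *Narrow*: only the participant whose confidentiality was breached is told. This is a natural reading, because the sentence directly follows the one on breach.

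**Applying both readings**

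| Situation | Broad reading | Narrow reading |
|---|---|---|
| A parent's own interview raises a concern about that parent's treatment of the child | Parent told | Parent told |
| A child's interview raises a concern about a participating parent | Child and parent told | Child told; nothing requires telling the parent |
| The same concern arises in a joint interview of child and parent | Both told | Not settled: both took part in the conversation |
| The concern is about someone who is not a participant | That person need not be told | That person need not be told |

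The first row carries the point. The parent is both the source of the information and the subject of the concern, so both readings give the same result, and no wording in the article allows the researcher to hold back. The second row depends on the reading and cannot carry the point alone. The third is an ambiguity that an exception would also resolve.

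**Is an exception supplied elsewhere?** The Consent, Interviews, Longitudinal interviews, and Anonymity and confidentiality subsections contain none. The trust protocols are not reproduced, so they may contain one, but the article applies them to escalation and not to the promise made to participants.

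**The case against.** **The article is a summary.** The ethics section says that it summarises, its figure is not available here, and operational detail normally sits in the full protocol or in trust procedures. This would answer a complaint about a missing detail. It does not answer a complaint about a promise made without qualification: if the full protocol or a trust procedure contains an exception, the published sentence disagrees with it and still needs changing.

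**Trust protocols may govern disclosure in practice.** A disclosure results from an escalation that must follow those protocols, so they may also decide who is told. That is plausible and may well be what the authors intend, but it is not what the sentence says.

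**The narrow reading protects the child who discloses.** This stands. A reader might infer that whenever a child reports a parent, the researcher must tell that parent. The article does not establish this; it is one possible reading. Nor does it say how often child and parent are seen together, which is left to their preference.

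**Observed concerns.** A reader might also infer that something the researcher sees, as opposed to hears, falls outside the rule, because the trigger refers to a participant's response while field notes include "reflections on the interview and observation of the family situation, environment, behaviour and any other interactions that may take place". The documents do not support this as an error. The trigger is not worded as exclusive, the section already reaches risk to other people, and nothing says that an observed concern would go unreported. Remarks noted after the recorder is off ("field notes made to include any additional comments from the child or family made once the audiorecording has stopped") can fairly be taken as part of a response. What remains is detail that a condensed article may omit.

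**Conclusion.** The point holds for the duty to inform. As written, the rule would have a participant who is the subject of a safeguarding concern told of the report and its recipient. This is certain when the concern comes from that person's own interview and possible when it comes from another family member's.

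The documents give no rate from which to size this. They expect breaches to be very rare, and a count of planned interviews would say nothing about how often a concern arises. There is no consequence for sample size, data collection or analysis. The weight comes from the potential severity for one child set against a very small change in wording, so the change should be made.

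The conclusion assumes that the article's sentence reflects what researchers will follow and participants will be promised. The full protocol, the trust protocols and the participant information sheet were not available to check this.

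**What to change.** Make the last sentence of Serious concerns and safeguarding subject to the trust process that the subsection already invokes. For example: *The participant whose confidence is broken will be told of the report and its recipient, unless the trust's safeguarding process advises that telling them could increase the risk to anyone.* This settles who is meant by participants, keeps openness as the default, and leaves the decision to withhold with the trust process, not the lone interviewer.

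Use the same wording in the participant information sheet and the consent discussion, since a promise given at consent is hard to depart from later. Check the full protocol and trust procedures for an existing exception and align the texts.

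Optionally, name field-note observations as a possible source of concern in the first sentence. This is a clarification, not a correction.

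The drafting cost is one clause and a matching line in the information sheet. The real cost is some loss of openness: a few participants may not be told of a report, or may be told later than now promised.
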